## Discussion

The present protocol paper describes the design of a single blind controlled trial. The aim of our study is to investigate whether additional therapy time focused on muscle strengthening, sitting balance and reach, getting up from a chair and walking has a positive effect on cognition, mood and activities of daily living (ADL) in stroke patients who rehabilitate on rehabilitation units of nursing homes. The study gives insight into how the care of elderly stroke patients in nursing homes might be improved so that patients have a better chance of independent living. When positive effects will be found this study can guide policy makers and practitioners on how to implement higher quality care on rehabilitation wards of nursing homes.

The strength of the study is that 1) interventions from the evidence based Clinical Nursing Rehabilitation Stroke Guideline are implemented in the rehabilitation care of older stroke patients. This implementation will significantly increase the time spent on therapeutic activities without extra therapists needed, 2) the role of nurses can shift towards a more therapeutic one, 3) we examine if an increase in therapeutic time has a beneficial effect on cognition, mood, and ADL. These factors are of great importance for rehabilitation success in stroke patients. Possible limitations of our study are 1) the high rate of drop-out due to illness or death of this frail patient group, 2) the convenience sample causing a possible selection bias, 3) the limited intervention time before patients are discharged from the rehabilitation units.

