### Randomisation

A convenience sample will be taken of patients who rehabilitate in the selected nursing homes in the period of April 2012 until April 2015 and are willing to participate.

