### Sample size

The sample size has been calculated by using the statistically power analysis program G Power. The estimated effect-size comes from a study reporting the effect of physical activity on cognition in patients with stroke (*d’* = 0.30) [27]. Taking into account a type one error of 0.05 (α = 0.05), a power of 0.80 (β = 0.08), three repeated measurements and two groups, a sample size of 138 patients is required, i.e. 69 persons in each group. Taken a dropout of 10% into account, a sample size of 81 persons in each group is required.

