### Data-analysis

Descriptive analysis on all the patient characteristics at baseline is performed. A t-test for independent groups will be used to check for comparability between the intervention and control group at baseline. A repeated-measures multivariate analysis of variance (MANOVA) will be applied to assess possible effect of increased therapeutic time over various test moments (baseline, 8 weeks and at the moment of discharge). The level of significance is 0.05. The SPSS-PC version no. 20 will be used for data-analyses (SPSS Inc., Chicago, IL, USA).

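### The plan expects high loss to illness or death, allows for 10%, and names only a MANOVA that in standard form drops incomplete patients, so unequal loss could bias the result in either direction

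*Protocol article*

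**What the plan says.** All references are to the protocol article.

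- **Discussion:** the possible limitations include "the high rate of drop-out due to illness or death of this frail patient group". No figure is attached.
- **Sample size:** "a sample size of 138 patients is required, i.e. 69 persons in each group", and then "Taken a dropout of 10% into account, a sample size of 81 persons in each group is required".
- **Data-analysis:** "A repeated-measures multivariate analysis of variance (MANOVA) will be applied to assess possible effect of increased therapeutic time over various test moments", namely baseline, 8 weeks and discharge, in SPSS 20. No other analysis of effect is named.
- **Procedure:** neuropsychologists test cognition and mood at those three times, and nursing staff score the Barthel Index weekly. The one rule for an absent 8-week assessment concerns patients discharged before 8 weeks, for whom discharge becomes the post measurement. Death, transfer and illness are not covered by that rule.
- **Randomisation:** "A convenience sample will be taken of patients who rehabilitate in the selected nursing homes". The group follows from the home in which a patient stays.

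**The concern.** The article predicts substantial loss for reasons tied to patients' health, but neither the planned number nor the chosen method responds to that prediction. A repeated-measures MANOVA in its usual form analyses only patients with a score at every occasion entered. A patient tested at baseline and at 8 weeks who then dies contributes nothing, although two of the three scores exist.

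Loss through illness or death is unlikely to be unrelated to cognition, mood or ADL. If its frequency, or the kind of patient lost, differs between the two pairs of homes, the completers are selected differently in the two groups. Because the groups are formed by home from a convenience sample, equal frailty and equal loss cannot be taken for granted. The article says that positive effects could guide policy makers and practitioners, so it matters whether the reported contrast describes all enrolled patients or only those who could be retested throughout.

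**Working it through.** **1. The plan's own allowance for loss**

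Inputs: 69 per group before loss, 10% loss, 81 per group after (Sample size).

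- Dividing by the retained share: 69 / 0.90 = 76.7, so 77 per group.
- Multiplying instead: 69 × 1.10 = 75.9, so 76 per group.
- Loss implied by the printed figure: 1 − 69/81 = 0.148, about 15%.

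The 81 is not reproduced by 10% loss. It does give more room than 10% would, but the article gives no reason for this.

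The 138 was not reproduced either. A two-sided comparison of two means with d = 0.30, alpha 0.05 and power 0.80 needs 2 × (1.960 + 0.842)² / 0.30² = 174.5, so 175 per group. A repeated-measures calculation depends on the correlation between occasions, which is not stated. This point does not depend on the 138, and 69 per group is taken as given below.

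**2. What a higher loss would leave**

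The Discussion gives no rate, so 20% and 30% are assumptions.

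| Loss | Left from 81 per group | Needed to keep 69 per group |
|---|---|---|
| 10% | 81 × 0.90 = 72.9 | 69 / 0.90 → 77 |
| 20% | 81 × 0.80 = 64.8 | 69 / 0.80 → 87 |
| 30% | 81 × 0.70 = 56.7 | 69 / 0.70 → 99 |

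Above about 15% loss, a completers' analysis falls below the plan's own requirement.

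**3. Who leaves the analysis**

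- *Cognition and mood* need a patient who can be tested or answer a questionnaire. Death, transfer and serious illness all remove the patient.
- *Barthel Index* is rated by nurses every week. A sick patient still on the unit can be scored, so it is death or transfer that ends the series.

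**4. Size of the possible bias**

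Let p be the loss rate in a group, and let D be how much worse the lost patients would have changed from baseline than the completers, in SD units. If C is the completers' mean change, the mean for all patients is (1 − p)C + p(C − D) = C − pD. Completers therefore overstate the group mean by pD, and the contrast is biased by

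bias = p(intervention) × D(intervention) − p(control) × D(control).

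With the same D in both groups this is the difference in loss rate times D. All inputs below are assumptions.

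| Difference in loss | D (change) | Bias | Share of d = 0.30 |
|---|---|---|---|
| 0 points | any | 0 | 0% |
| 10 points | 0.5 | 0.10 × 0.5 = 0.05 SD | 17% |
| 10 points | 1.0 | 0.10 × 1.0 = 0.10 SD | 33% |
| 15 points | 0.5 | 0.15 × 0.5 = 0.075 SD | 25% |
| 15 points | 1.0 | 0.15 × 1.0 = 0.15 SD | 50% |

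The sign follows the group with more loss. More loss in the intervention homes flatters the intervention, and more in the control homes does the reverse. D counts only the deficit that arises after baseline. If lost patients would have scored 0.5 SD lower at follow-up but were already 0.5 SD lower at baseline, D = 0.5 − 0.5 = 0 and the bias in change vanishes. The last column also assumes that the SD behind d = 0.30 is the one used for D.

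**The case against.** **A condensed article may leave this to fuller documents.** Missing-data rules, safety recording and sensitivity analyses often stand in a full protocol or analysis plan. This is right, and the absence of an adverse-event section is not raised here. What remains is what the article itself fixes: the named method, the 10%, and a Discussion that expects more.

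**The article never says complete cases.** This is also right. The exclusion follows from the standard form of the named method, and imputation beforehand is neither stated nor ruled out. Using discharge as the post measurement also helps early leavers, but it does nothing for patients who die or become too ill.

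**The loss is a disclosed limitation, and the inputs are invented.** The rates and deficits are indeed assumptions. Patients too ill to take part are excluded at entry, and the exercises are adapted to each patient's level, so nothing shows that loss will be higher with the intervention. This limits what can be said about size and direction. It does not remove the mismatch between the expected loss and the method.

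**A stronger inference is tempting:** that harm from the added exercise would drop out of the results and appear as benefit. The documents do not support it. The Discussion attributes the loss to the frailty of the patients, not to the exercises. No passage points to more loss in the intervention homes. Harm that does not cause drop-out stays in the scores, and the Barthel Index can still be recorded in a sick patient on the unit.

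**Conclusion.** The point holds in a limited form. The article expects a high rate of loss from illness or death, budgets for 10%, and names one analysis that in standard form discards patients with any analysed occasion missing. The completers' contrast can then be biased in either direction if loss, or the kind of patient lost, differs between the groups.

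The illustrative size is 0.05 SD for a 10-point difference in loss and a 0.5 SD deficit in change, and up to 0.15 SD across the assumed range. It is zero when loss and deficit are equal in the two groups. These figures show what could happen and are not estimates for this trial. The larger ones need a deficit that arises wholly after baseline.

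Separately, and without any assumption about loss by group, 10% does not fit the Discussion and does not yield 81. This should be corrected, but it does not invalidate the design.

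**What to change.** 1. **Analysis.** In Data-analysis, replace the MANOVA with a likelihood-based repeated-measures model that keeps every patient with a baseline and any later score.
2. **Losses.** Report the number lost by group and by cause (death; illness or transfer; other) next to the primary result.
3. **Sensitivity analysis.** Add one analysis that gives patients lost to illness or death an unfavourable score, and state any conclusion of benefit in light of it. This is needed because the model alone assumes missingness at random and does not repair loss through death. Scoring the dead changes the question asked, so it belongs beside the main result and not in place of it.
4. **Sample size.** Reconcile the 10% with the Discussion. State the loss rate actually planned for and derive the number from it: 77 per group at 10%, or about 15% if 81 is kept.

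A rule that forbids a conclusion of benefit unless there is no excess of such events is not proposed. With two unrandomised homes per group, an excess could reflect the homes and not the treatment.

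The cost is a little more analysis work and a record of why each patient left. A favourable result may become less favourable.
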